### Aims

The aims of this study are as follows:

To test the effectiveness of a co-designed help-seeking program (the Helipad program) on increasing professional help-seeking intentions (primary outcome) in employees in a workplace setting at posttest (primary end point) and the 6-month follow-upTo determine whether the program reduces mental illness stigma and improves help-seeking attitudes and behavior, mental health literacy, mental health symptoms, quality of life, and functioning (secondary outcomes) relative to the control condition at the 6-month follow-upTo explore factors that facilitate broader implementation of the co-designed programTo explore the cost-effectiveness of the co-designed program compared to the active control condition from the health sector and societal perspectives at the 6-month follow-up

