#### Secondary Hypotheses (Aim 2)

Hypothesis 2: Mental illness stigma will be lower and mental health literacy and help-seeking attitudes will be higher in the Helipad co-designed interactive program condition relative to the control condition (standard psychoeducation only) at posttest.Hypothesis 3: Help-seeking behavior will be greater in the Helipad co-designed interactive program condition among people with elevated symptoms of depression or anxiety relative to the control condition (standard psychoeducation only) at the 6-month follow-up.Hypothesis 4: Symptoms of mental ill-health will be lower and quality of life and functioning will be higher in the Helipad co-designed interactive program condition relative to the control condition (standard psychoeducation only) at the 6-month follow-up.

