#### Secondary Outcomes

Effectiveness will be compared between the Helipad co-designed interactive program condition and the standard psychoeducation web-based program condition for mental illness stigma, mental health literacy, and help-seeking attitudes (hypothesis 2), which will be assessed, respectively, based on reduced mental health stigma (Stigma and Self-Stigma Scales [40]), increased mental health literacy (Anxiety Literacy Questionnaire [A-Lit] and Depression Literacy Questionnaire [D-Lit] composite measure [41,42]), and increased help-seeking attitudes (Attitudes Toward Seeking Professional Psychological Help Scale-short form [43]) over time relative to the control condition.

In addition, we will examine the comparative effectiveness of the Helipad co-designed interactive program condition and the standard psychoeducation web-based program condition on reducing symptoms of mental ill-health and increasing quality of life and functioning (hypothesis 4). This will be determined based on reduced symptoms over time of depression (Patient-Reported Outcomes Measurement Information System [PROMIS] Depression short form scale [44]), anxiety (PROMIS Anxiety short form scale [44]), and general psychological distress (Distress Questionnaire-5 [DQ5] [45]) and increased scores on the Recovering Quality of Life (ReQoL-10) Questionnaire [46] and increased work and activity functioning (Work Productivity and Activity Impairment [WPAI] questionnaire [47]).

Finally, the relative effects of the program on increasing help-seeking behavior (hypothesis 3) will be assessed by the proportion of participants who reported seeking help from a professional source (defined as a psychologist or counselor, a psychiatrist, a family doctor or general practitioner [GP], or an EAP) in the past 6 months. We anticipate that this will be greater in the Helipad co-designed interactive program group among people with elevated symptoms of depression or anxiety relative to the control condition (standard psychoeducation only).

The primary end point for changes in mental health literacy is the posttest assessment, while for the other secondary outcomes, the 6-month follow-up assessment will be the primary end point as these outcomes take longer to elicit change.

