#### Assessments and Blinding

Table 1 presents the trial measures and assessment time points. Assessments will occur at baseline (pretest), posttest, and 6 months after the program is completed. The trial will be triple blinded. Participants will be blinded as far as possible to the condition; they will only be informed that their workplace has been randomized to receive one of two programs: (1) an enhanced interactive mental health education program or (2) a standard written psychoeducation program. We will not provide participants with information about which program is expected to be the most effective. The statistician who will perform the analyses will be blinded to condition allocation (triple blind). Finally, assessments will also be blinded, as they rely on participants independently completing self-report measures on the web.

**Table 1 table1:** Assessment time points for the Helipad cluster randomized controlled trial of a brief workplace training program to support help-seeking for mental ill-health.

Construct	Measure	Presurvey	Postsurvey	6-month follow-up survey
Gender	What is your gender?	✓		
Age	What is your age?	✓		
Language spoken at home	What language do you usually speak at home?	✓		
Ethnicity	How would you describe your ethnicity?	✓		
Education	What is the highest level of education that you have completed?	✓		
Employment status	What is your current employment status?	✓		
Industry	What industry are you employed in?	✓		
Help-seeking intentions	GHSQ^a^	✓	✓	✓
Help-seeking attitudes	ATSPPH-SF^b^	✓	✓	✓
Help-seeking behavior: service use type and quantity	AHSQ^c^	✓		✓
Mental illness stigma	(SASS^d^-modified)	✓	✓	✓
Mental health literacy	D-Lit^e^ or A-Lit^f^ composite	✓	✓	✓
Depression symptoms	PROMIS^g^ Depression-Short Form	✓		✓
Anxiety symptoms	PROMIS Anxiety-Short Form	✓		✓
General psychological distress	DQ5^h^	✓		✓
Work and activity impairment	WPAI^i^	✓		✓
Quality of life	ReQoL-10^j^	✓		✓
Adverse events	Did you have any unexpected or negative experiences that might be related to completing this program?		✓	✓
Intervention acceptability	AIM^k^		✓	
Intervention appropriateness	IAM^l^		✓	
Intervention feasibility	FIM^m^		✓	
Debriefing	Explanation of study			✓
Interview	Interest in an interview		✓	

^a^GHSQ: General Help-Seeking Questionnaire.

^b^ATSPPH-SF: Attitudes Toward Seeking Professional Psychological Help Scale-short form.

^c^AHSQ: Actual Help-Seeking Questionnaire.

^d^SASS: Stigma and Self-Stigma Scales.

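### Stigma and help-seeking attitudes have two conflicting decision time points: posttest in Hypothesis 2, 6 months in the Secondary Outcomes section and Aim 2

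*Protocol article*

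**What the plan says.** Three places in the protocol article give a time point for the secondary outcomes.

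- **Secondary Hypotheses (Aim 2).** Hypothesis 2 predicts an advantage over the control arm: "Mental illness stigma will be lower and mental health literacy and help-seeking attitudes will be higher in the Helipad co-designed interactive program condition". Its time point is posttest, as shown where its text runs into the next hypothesis: "standard psychoeducation only) at posttest.Hypothesis 3: Help-seeking behavior will be greater".
- **Secondary Outcomes.** This section assigns the same three outcomes to that hypothesis: "for mental illness stigma, mental health literacy, and help-seeking attitudes (hypothesis 2". It then splits them. For literacy, "The primary end point for changes in mental health literacy is the posttest assessment". The rest are treated differently, on the ground that they are slower to change: "while for the other secondary outcomes, the 6-month follow-up assessment will be the primary end point". Stigma and attitudes fall under the rest.
- **Aims.** Aim 2 takes in every secondary outcome, literacy included ("program reduces mental illness stigma and improves help-seeking attitudes and behavior, mental health literacy, mental health symptoms, quality of life, and functioning (secondary outcomes"), and places the whole list at the 6-month follow-up.

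On the schedule, Assessments and Blinding states: "Assessments will occur at baseline (pretest), posttest, and 6 months after the program is completed". Table 1 ticks stigma, attitudes and literacy at all three surveys.

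**The concern.** A secondary hypothesis should have one contrast that decides it. Here two of the three Hypothesis 2 outcomes have two, and both will exist in the data. Posttest comes straight after a program of about 20 minutes; follow-up is 6 months later. The two contrasts can easily disagree. An immediate shift in stigma that fades would support Hypothesis 2 as worded and fail under the Secondary Outcomes section. A slow effect would do the reverse. In either case the authors could point to published text that pre-specified the favourable result.

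There is also a downstream consequence. The Data Analysis section says that further incremental cost-effectiveness ratios will be calculated for secondary outcomes on which the program shows an effect. For stigma and attitudes, whether such a ratio is produced can depend on which time point counts.

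**Working it through.** The plan gives no figure for this point, so the main check is to set the texts side by side.

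| Outcome | Aim 2 | Hypothesis | Secondary Outcomes section | Surveys after baseline (Table 1) |
|---|---|---|---|---|
| Stigma | 6 months | posttest (H2) | 6 months | posttest and 6 months |
| Help-seeking attitudes | 6 months | posttest (H2) | 6 months | posttest and 6 months |
| Mental health literacy | 6 months | posttest (H2) | posttest | posttest and 6 months |
| Help-seeking behavior | 6 months | 6 months (H3) | 6 months | 6 months |
| Symptoms, quality of life, functioning | 6 months | 6 months (H4) | 6 months | 6 months |

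The last two rows agree throughout. In the first two, the hypothesis conflicts with both other places. In the literacy row only the summary aim is out of line. The schedule cannot settle the first three rows, because all three measures are taken at both times. The Data Analysis section does not settle them either: it describes a repeated-measures mixed model using all available data and does not say which contrast decides a hypothesis.

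**Size of the freedom this leaves.** Inputs: two contrasts per outcome, and a two-tailed 5% level. The article states that level only for the sample size (Power and Recruitment); applying it to secondary outcomes is an assumption.

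- At least one significant result in either direction under no effect, independent contrasts: 1 − 0.95² = 1 − 0.9025 = 0.0975, or 9.75%, against 5% for one test.
- At least one significant result in the hypothesised direction: each two-sided test spends 0.05 / 2 = 0.025 on that side, so 1 − 0.975² = 1 − 0.950625 = 0.0494, or about 4.9%, against 2.5% for one test.

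Both are ceilings for non-negatively correlated contrasts. The two contrasts use the same people and the same scale, so they are likely to be positively correlated. The article gives no correlation, so the values below are assumptions. They come from the bivariate normal distribution with critical value 1.96.

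| Assumed correlation | Either direction | Hypothesised direction |
|---|---|---|
| 0 | 9.75% | 4.9% |
| 0.3 | 9.5% | 4.8% |
| 0.5 | 9.1% | 4.5% |
| 0.7 | 8.3% | 4.2% |
| 0.8 | 7.8% | 3.9% |

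**Number of entries to change under each resolution.** Following the Secondary Outcomes section: two outcomes in Hypothesis 2 plus one (literacy) in Aim 2, so 3. Following Hypothesis 2: three outcomes in Aim 2 plus two in the Secondary Outcomes section, so 5.

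**The case against.** The best defence is that the hypotheses are only expectations and that the Secondary Outcomes section alone sets end points, since it is the only place that calls a time point primary for a secondary outcome. This is possible but strained. Hypothesis 2 names its time point, and the Secondary Outcomes section refers back to Hypothesis 2 by number before assigning two of its outcomes elsewhere. The reason it gives, that these outcomes change slowly, runs against a posttest test. Nor can the conflict be left to a separate analysis plan: this is contradictory text, not missing detail, and a plan that chose one time point would still contradict part of the article.

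Several stronger inferences are not supported:

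- **That literacy is equally undecided.** It is not. The hypothesis and the Secondary Outcomes section agree on posttest; only Aim 2, which gives one time point to a long list, differs.
- **That the false-positive rate is 9.75%.** That figure is a ceiling, it counts results in either direction, and it arises only if the choice is made after seeing both contrasts.
- **That the lack of a 6-month attrition figure is part of the fault.** The sample size rests on the primary outcome at posttest, and the mixed model uses participants with missing time points.
- **That Hypothesis 2 must prevail, or is the smaller edit.** It needs more changes and overrides the only rationale the article gives.
- **That the registry entry is wrong.** It is not among the documents.

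**Conclusion.** The contradiction stands for mental illness stigma and help-seeking attitudes. Two incompatible decision time points are stated for the same hypothesis, and nothing else in the article settles which governs. For literacy there is a lesser drafting inconsistency, confined to Aim 2.

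The consequence is moderate. The affected outcomes are secondary. The primary outcome has posttest as its end point throughout, and Hypotheses 3 and 4 match both the Secondary Outcomes section and Aim 2. For each of the two affected outcomes, the chance of a false result in the hypothesised direction could rise from 2.5% to at most about 4.9% (either direction: from 5% to at most 9.75%). This assumes two-sided 5% tests and a free choice after both results are known. The finding does not rest on these figures; the conflict in the text is sufficient.

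**What to change.** Before unblinded results are seen, name one primary time point for each secondary outcome, label the other as supporting, and state the same choice in the Aims, the Secondary Hypotheses and the Secondary Outcomes section. Either of two resolutions would do:

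1. Follow the reasoning in the Secondary Outcomes section: 6 months for stigma and attitudes, posttest for literacy. Amend Hypothesis 2 for the first two and Aim 2 for literacy.
2. Follow Hypothesis 2: posttest for all three. Amend Aim 2 and the Secondary Outcomes section, including its stated reason as it applies to stigma and attitudes.

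The investigators should choose on substantive grounds and record the date and reason. Help-seeking behavior, symptoms, quality of life and functioning stay at 6 months. The cost is wording in two places under either option; no data collection, assessment or sample size changes. The registry record should be checked for agreement.

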### Data Analysis

An intention-to-treat approach to account for missing data of the mixed model repeated measures ANOVA (continuous data) or mixed effects logistic regression (binary data) will be used, adjusting for intraclass correlation to account for clustering effects within each site. Mixed models include all available data and account for within-individual variability, including those participants with missing data points, under the missing-at-random assumption [48].

Exploratory analyses will examine evidence for moderators or mediators of outcome and will be reported separately from the primary and secondary outcomes. Implementation outcomes at 6 months will be separately examined using description statistics, including *t* tests (2-tailed). The economic analysis will examine cost-effectiveness from the health sector and societal perspectives. The cost of the Helipad intervention and the active control program will be estimated using microcosting methods. Service use data will be limited in this study to health care professional visits or services accessed (internet program and helpline) specifically for mental health. The additional costs of health care resource use will be operationalized as the number of contacts with health professionals collected on the Actual Help-Seeking Questionnaire [49] (psychologist or counselor, psychiatrist, family doctor or GP, EAP, phone helpline, and internet-based treatment program). Lost productivity will also be evaluated in societal perspective costs as assessed through the WPAI questionnaire [47] and valued using the human capital approach. The ReQoL-10 Questionnaire [46] will be used to calculate utility values and quality-adjusted life years (QALYs) using the area under the curve method. Differences in costs between trial groups will be compared to the differences in QALYs through an incremental cost-effectiveness ratio (ICER) because of the inherent value-for-money connotations associated with cost-effectiveness ratios using QALYs. Additional ICERs using secondary outcomes will be calculated where the Helipad intervention is found to have an effect. Nonparametric bootstrapping will be used to determine CIs for ICERs.

In addition, we will report proportions of participants who improve, decline, and do not change on outcome measures. Automatically collected aggregate use data will also be analyzed, including information on how many participants access each page, location, average time on each page, video view count data, and clicks to external links.

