## Methods

### Trial Design

A 2-arm cluster RCT will test whether the Helipad co-designed interactive program increases help-seeking intentions in employees in workplaces more than the standard psychoeducation-alone program. Workplaces will be randomly allocated using minimization processes to either (1) the active intervention condition comprising the Helipad program or (2) an active control condition (a web-based time-matched standard psychoeducation program). Help-seeking intentions will be assessed at the individual level accounting for clustering by workplace. Self-report assessments will be conducted on the web at preintervention, immediately postintervention, and at the 6-month follow-up. This study protocol addresses the Standard Protocol Items: Recommendations for Interventional Trials (SPIRIT) checklist [30].

The flow of participants through the study is presented in Figure 1.

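### The implementation t tests are set at 6 months, when the three implementation scales are not collected, and carry no clustering adjustment; the additional ICERs are selected on the result

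*Protocol article*

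**What the plan says.** **Implementation analysis.** The Data Analysis section of the protocol article states: "Implementation outcomes at 6 months will be separately examined using description statistics", and the same sentence names two-tailed t tests among these. It does not say which groups the t tests compare.

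**Implementation measures.** The section on implementation measures names three four-item scales: AIM, IAM and FIM. It adds adherence, attrition and factors associated with them, and refers to follow-up interviews. In Table 1 the row "Intervention acceptability" and the two rows below it, for appropriateness and feasibility, are each ticked once, under the postsurvey.

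**Clustering.** Trial Design says: "Help-seeking intentions will be assessed at the individual level accounting for clustering by workplace". In Data Analysis, the mixed ANOVA and mixed logistic models "will be used, adjusting for intraclass correlation to account for clustering effects within each site". Nothing similar is attached to the t tests.

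**Additional ICERs.** Data Analysis also states: "Additional ICERs using secondary outcomes will be calculated where the Helipad intervention is found to have an effect". The cost-per-QALY ratio in the preceding sentence carries no such condition.

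**The concern.** There are three issues, all in stated text rather than in detail left to an analysis plan.

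1. The analysis time point and the collection schedule disagree for the three scales that are the natural subject of a t test.
2. The plan allocates workplaces and models clustering for effectiveness, then names for the implementation outcomes a test that treats employees as independent. If that test compares arms, its standard error is too small and its p values too optimistic.
3. An additional cost-effectiveness ratio is produced only if its own denominator, the effect, has come out favourably. A reader would see a selected set of ratios.

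At stake is how far the quantitative results for aims 3 and 4 can be trusted. The primary outcome and the secondary effectiveness outcomes are not involved.

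**Working it through.** **Time point.** Set side by side:

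| Item | Where | Time point |
|---|---|---|
| Implementation outcomes, t tests | Data Analysis | 6 months |
| AIM, IAM, FIM | Table 1 | postsurvey only |
| Attrition | Implementation measures | observable at 6 months |
| Interviews | Follow-Up Interview | after the 6-month period |

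The 6-month analysis therefore has no data on the three scales, though it does have data on attrition.

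**Type I error of an unadjusted between-arm t test.** The article gives no error rate for these tests, so there is no figure to reproduce. Inputs from Power and Recruitment: ICC 0.02 (assumed there for the primary outcome), clusters of 25 to 35, 15% loss from pre- to postintervention, two-sided 5%.

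- Retained cluster size: 25 × 0.85 = 21.25; 35 × 0.85 = 29.75.
- Design effect, DE = 1 + (m − 1) × ICC: 1 + 20.25 × 0.02 = 1.405; 1 + 28.75 × 0.02 = 1.575.
- The standard error is understated by √DE: 1.185 and 1.255.
- True type I error = 2 × [1 − Φ(1.96/√DE)]: 9.8% and 11.8%.

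Simulated unadjusted t tests on null clustered data at ICC 0.02 (10,000 runs each) agree: 9.2% with 36 workplaces of 21, and 11.6% with 30 workplaces of 30.

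The document gives no ICC for AIM, IAM or FIM, so the result is shown over a range:

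| Assumed ICC | DE, m = 21.25 to 29.75 | True type I error |
|---|---|---|
| 0.005 | 1.10 to 1.14 | 6.2 to 6.7% |
| 0.01 | 1.20 to 1.29 | 7.4 to 8.4% |
| 0.02 | 1.41 to 1.58 | 9.8 to 11.8% |
| 0.05 | 2.01 to 2.44 | 17 to 21% |

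**Selection of additional ICERs.** The ratio is ΔC/ΔE, where ΔC is the difference in cost and ΔE the difference in effect. If it is reported only when ΔE has passed some test of having an effect, the reported ΔE values are on average too large. For a given positive ΔC, overstating ΔE by a factor f divides the ratio by f and makes the programme look cheaper per unit of benefit. The document gives no standard errors or expected effects for the secondary outcomes, so f cannot be estimated; only the direction is clear.

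**The case against.** **What stands.** The text presents the t tests as descriptive and does not say that they compare arms. If they contrasted, say, completers with non-completers within the same workplaces, the design-effect calculation above would not apply in this form. The ICC of 0.02 belongs to the primary outcome, and the article calls it conservative. Aim 3 has no hypotheses and is explored with interviews, so it does not depend on these p values. The condition on the additional ICERs is declared openly in advance, and aim 4 is labelled exploratory. All this limits the weight of the point. It does not remove the schedule mismatch, the absence of a clustering term from a named test, or the selection rule.

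**What a reader might infer, but the documents do not support.**

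- *That the ICER bootstrap ignores workplaces.* The article says only "Nonparametric bootstrapping will be used to determine CIs for ICERs". It does not give the resampling unit, a detail that a condensed article commonly leaves to the full plan. No ICC for costs or QALYs is given either, so no widening of the ICER intervals can be calculated.
- *That ICER intervals must be replaced by net benefit.* This is a choice of presentation. The article already ties the judgement to willingness-to-pay thresholds under Exploratory Hypotheses (Aim 4).
- *That there are no implementation data at all at 6 months.* Attrition can be observed then.
- *That the cost-effectiveness conclusion as a whole is selected on the result.* The cost-per-QALY ratio is unconditional.

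**Conclusion.** The point holds in limited form. The mismatch between Data Analysis and Table 1 is certain for AIM, IAM and FIM and needs no assumption. The clustering point is conditional: if the t tests compare arms and the ICC is 0.02, a nominal 5% test operates at about 10 to 12%. Over assumed ICCs of 0.005 to 0.05 the rate runs from about 6% to 21%, above 5% throughout. The selection of additional ICERs is explicit and its direction is clear, but its size cannot be derived from the document. The consequences are confined to exploratory aims 3 and 4; the primary analysis, the secondary effectiveness analyses and the main cost-per-QALY ratio are unaffected. The changes are worth making because they are cheap, not because the trial's main conclusion is at risk.

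**What to change.** 1. State that AIM, IAM and FIM are analysed at posttest, and keep 6 months only for indicators observable then, such as attrition.
2. For any comparison of arms on these scales, replace the t test with the mixed model already planned, with a random effect for workplace. Say what is being compared.
3. Name the secondary outcomes for which additional ICERs will be calculated, before any outcome data are seen, and report them whatever the effect turns out to be.

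The cost is a few lines of wording and analysis code, and a little more reporting. Intervals for the arm differences on the three scales become wider, by about 19 to 25% at the assumed ICC of 0.02 (√DE of 1.185 to 1.255). No new data collection and no change in sample size is required.

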### Trial Delivery

The trial will be delivered using a custom-designed website that will contain the 2 web-based programs. This website will allow self-report assessments, intervention materials, and email reminders to be delivered seamlessly to the participants. Furthermore, the website will collect and securely house the survey data collected. To streamline access and reduce the need for participants to create log-ins while maintaining security and confidentiality, participants will only need to provide an email to access the program.

If surveys or the program are discontinued, participants will be emailed a single reminder (at 48 hours if they discontinue any part of the preintervention, program, and postintervention survey and 1 week for the 6-month follow-up survey) with a unique link to access the program from their email account to continue from where they left to complete that part of the study. We expect most participants will complete the preintervention, program, and postintervention surveys in one 40-minute sitting. As such, we do not anticipate that these reminders will be needed frequently; however, given that people could discontinue the program or surveys, we have a method to reconnect them with the study.

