### Data Collection

#### Overview

Participants who agree to participate in the trial by clicking the link will be asked to provide an email address and complete a brief 10-minute baseline questionnaire. Following completion of the baseline questionnaire, participants will immediately be given access to the web-based program (approximately 20 minutes), which will be followed immediately by the 10-minute posttest questionnaire survey. The 10-minute follow-up survey link will be sent to participants via email 6 months after completion of their allocated condition.

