#### Quality of Life

To measure the impact of the program on quality of life and for the economic evaluation, we will use the ReQoL-10 Questionnaire [46], which is a validated measure and highly suitable for measuring recovery and quality of life in the mental health context. The ReQoL-10 comprises 11 items, including 10 focused on mental health and 1 focused on physical health. The mental health items assess the frequency experienced over the last week of the thoughts, feelings, or activities mentioned, such as “I could do the things I wanted to do” and “I felt lonely,” assessed on a scale from 0=none of the time to 4=most or all of the time. Negatively worded items are reverse scored. The 11th item assesses the severity of physical health problems, including “problems with pain, mobility, difficulties caring for yourself or feeling physically unwell” experienced on a 5-point scale from 4=no problems to 0=very severe problems. The scale has been validated, with Cronbach α ranging from 0.87 to 0.92 [46,56], and has been used in economic evaluations of mental health interventions [57]. A UK-derived value set will be used to calculate utility values at each time point. The area under the curve method will be used to calculate QALYs from utility values.

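### The two-point QALY puts half its weight on pre-intervention utility, and the stated between-group comparison names no adjustment for baseline utility

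*Protocol article*

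**What the plan says.** Everything here is in the protocol article.

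- **Schedule.** In Table 1 (Assessments and Blinding), the row "Quality of life ReQoL-10^j" is ticked for the presurvey and the 6-month survey; the postsurvey cell is empty.
- **Utilities and QALYs.** Under Measures, Quality of Life: "A UK-derived value set will be used to calculate utility values at each time point", and then "The area under the curve method will be used to calculate QALYs from utility values". Data Analysis repeats that the ReQoL-10 "will be used to calculate utility values and quality-adjusted life years (QALYs) using the area under the curve method".
- **Comparison.** Data Analysis: "Differences in costs between trial groups will be compared to the differences in QALYs through an incremental cost-effectiveness ratio (ICER". For uncertainty: "Nonparametric bootstrapping will be used to determine CIs for ICERs".
- **Horizon.** The last survey is sent "6 months after completion of their allocated condition" (Data Collection, Overview).
- **Adjustment.** Neither section mentions baseline utility as a covariate, and neither excludes it. The mixed models in Data Analysis are described for continuous and binary outcomes, not for QALYs.
- **Status.** Aims lists the economic question as one to explore. Exploratory Hypotheses (Aim 4) nevertheless states a direction: that the program will be cost-effective.

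**The concern.** With one utility before the program and one after, an area under the curve weights the two equally. A difference between arms that existed before anyone saw the program is then counted as QALYs gained or lost.

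Three features of the design make such a difference plausible:

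- Only 30 to 36 workplaces are allocated, and the minimization factors (workplace type, size, location) include no mental health measure.
- Workplace Recruitment seeks a mixture of general and high-risk workplaces, the latter chosen for exposures that may affect mental health. Risk status is not a balancing factor.
- Employees are invited and consent after their workplace has been allocated, so a difference need not be due to chance alone.

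Bootstrapping describes the uncertainty of whichever contrast is chosen; it does not take imbalance out of it. At stake are the size, and possibly the sign, of the ICER denominator, and precision that could be had from data already collected.

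**Working it through.** The article gives no QALY figure to reproduce, so the check starts from its stated method.

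**Inputs from the article:** two utility points; horizon T = 0.5 year; 36 workplaces of 25 (900 employees) or 30 of 35 (1,050); ICC 0.02. The ICC is given in Power and Recruitment for the primary outcome and is borrowed here for utility.

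**Assumptions not in the article:** utility SD 0.10 to 0.20, equal at both times; correlation r between presurvey and 6-month utility of 0.5 to 0.7; a 6-month effect of d = 0.1 for scale.

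**1. Weights.** QALY = T × (u0 + u6)/2 = 0.5 × (u0 + u6)/2 = 0.25 × u0 + 0.25 × u6. Presurvey utility has 50% of the weight.

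**2. Carry-over of a baseline difference.** If the arms differ by D0 at presurvey and a fraction p persists to 6 months, the unadjusted QALY difference contains 0.25 × D0 × (1 + p) with no program effect. For D0 = 0.01:

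| p | Carried into the incremental QALY |
|---|---|
| 0 | 0.0025 |
| 0.5 | 0.00375 |
| 1 | 0.005 |

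**3. Variance, individual level.**
- Unadjusted: SD² × (2 + 2r)/16.
- Adjusted for u0: SD² × (1 − r²)/16.
- Ratio: 2(1 + r)/[(1 − r)(1 + r)] = 2/(1 − r).

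| r | Variance ratio | SE ratio |
|---|---|---|
| 0.5 | 4.0 | 2.00 |
| 0.6 | 5.0 | 2.24 |
| 0.7 | 6.7 | 2.58 |

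**4. Chance imbalance.** SE of the baseline difference = SD × √(4 × DE/N), with DE = 1 + (m − 1) × 0.02.
- 36 workplaces of 25: DE = 1.48; √(4 × 1.48/900) = 0.0811. For SD 0.10 the SE is 0.0081, and × 0.25 gives 0.0020 QALY. For SD 0.20 it is 0.0162, and × 0.25 gives 0.0041 QALY.
- 30 workplaces of 35: DE = 1.68; √(4 × 1.68/1,050) = 0.0800, giving 0.0020 and 0.0040 QALY.

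This is the baseline term alone, before any persistence to 6 months and before loss to follow-up.

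**5. Scale of an effect.** d = 0.1 at 6 months is worth 0.25 × 0.1 × SD: 0.0025 QALY for SD 0.10 and 0.005 for SD 0.20. The baseline term's SE is therefore about 0.081/0.1 = 81% of that effect, whatever the SD.

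**6. A constructed example of a sign change.** The Helipad arm starts 0.02 lower in utility and ends 0.01 higher. The change from baseline favors it by 0.03. The unadjusted QALY difference is 0.25 × (−0.02 + 0.01) = −0.0025. Adjusted with a slope of 0.6 on presurvey utility, it is 0.25 × (0.01 + 0.6 × 0.02) = +0.0055.

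**The case against.** The strongest objection is that the article is silent on adjustment and has not decided against it. A regression-adjusted difference is still a difference in QALYs between groups, so the ICER sentence is compatible with either approach. Model details of this kind often sit in an analysis plan or health economic plan that is not shown, and the article says the economic analyses will be published separately. This stands to the extent that no one should read the article as ruling adjustment out. It does not dispose of the point. The two-point schedule, the area-under-the-curve rule and the group-difference ICER are all stated, and following them literally gives the weaker contrast.

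Three stronger readings are tempting but not supported:

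- **That half of each QALY is noise or imbalance.** This confuses weight with error. Baseline utility is a real level of health and cancels between comparable arms in expectation. Only the between-arm difference in it, and the variance of that difference, do harm.
- **That costs have the same defect.** Help-Seeking Behavior sets the service-use recall at the past 6 months, and the follow-up survey comes 6 months after program completion, so follow-up contacts cover the post-intervention period. Nothing in the article gives presurvey contacts a weight in the 6-month cost.
- **That the schedule needs a ReQoL-10 at posttest.** Most participants are expected to "complete the preintervention, program, and postintervention surveys in one 40-minute sitting". A utility taken then would say almost nothing about the course over 6 months.

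It is also fair to say that the sizes rest on an SD, an r and an effect the article does not give, and on an ICC stated for another outcome. The 15% attrition in Power and Recruitment runs only from pre- to postintervention, so it is not used here; losses by 6 months would widen the standard errors.

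**Conclusion.** The point holds as a weakness in the estimator as stated, not as a proven omission from the full analysis plan. The 50% baseline weight and the 0.25 carry-over follow from the article alone. The variance ratio of 2/(1 − r) is exact algebra for individuals with equal variances at the two times; its value of 4.0 to 6.7 depends on the assumed r. The comparison of chance imbalance with a d = 0.1 effect depends on the borrowed ICC and full baseline numbers, while the absolute QALY figures also depend on the assumed SD. Whether a baseline difference will actually arise cannot be known from the documents. The consequence is confined to the exploratory Aim 4; no primary or secondary effectiveness conclusion depends on it. It is still worth correcting, because the ICER will be used to judge a directional hypothesis and the remedy uses a covariate already collected.

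**What to change.** In Data Analysis, state that the incremental QALY is estimated by regressing each participant's area-under-the-curve QALY on arm and presurvey ReQoL-10 utility, accounting for clustering by workplace. State that this adjusted difference is the ICER denominator and is re-estimated in every bootstrap replicate, with the bootstrap resampling workplaces rather than individual employees. If an unshown economic plan already says this, a cross-reference is enough.

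Adjusting incremental cost for presurvey service contacts and presurvey productivity loss is an optional gain in precision and balance, not a correction of this defect.

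The cost is a sentence or two of analysis text and little programming. No new data, survey time or change to the schedule is needed.
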